## Abstract

**Background:**

Studies suggest that 40% to 65% of stroke survivors develop chronic poststroke pain (CPSP), which severely affects their quality of life and mental health. Empirical evidence suggests that existing treatments often fall short, underscoring the need for innovative, integrative interventions. Virtual reality (VR) seems to provide valuable tools in stroke rehabilitation. Also, contextual-behavioral psychological approaches, such as acceptance and commitment therapy (ACT), offer promising pain management and mental health resources, which seem to be feasible in VR formats. However, their combined application in CPSP remains unexplored.

**Objective:**

This study protocol describes the VR-ACT study, which will test the feasibility and preliminary efficacy of an 8-week VR-ACT program for CPSP.

**Methods:**

This pilot randomized controlled trial (N=30) will compare a VR-based ACT intervention with a sham VR control. The study will follow a mixed methods approach. Quantitative outcomes include pain intensity, psychological symptoms, and quality of life (via self-report measures), and brain network connectivity of the Triple Network (via functional magnetic resonance imaging). Feasibility will be evaluated through adherence, engagement, and acceptability. Qualitative feedback will be collected postintervention.

**Results:**

This study was funded by the Portuguese Foundation for Science and Technology in February 2025. Data collection is expected to start in December 2025 and end in June 2026. Results are expected to be published in the fall/winter of 2026/2027.

**Conclusions:**

This trial is expected to support the hypothesis that a VR-delivered ACT program is a feasible, acceptable, and potentially effective tool to support pain self-management and mental health in patients with CPSP, thereby laying the groundwork for larger multicenter trials.

## Introduction

Chronic poststroke pain (CPSP: pain lasting for more than 3 mo after stroke) affects 40% to 65% of stroke survivors [1] and can develop within 6 months after stroke [2]. CPSP substantially impacts patients’ quality of life, increases the likelihood of functional dependence and cognitive decline, and increases the risk of depression, anxiety, and fatigue [3]; it is also a predictor of suicidality after stroke [4]. Pain is experienced up to 10 years after stroke [5], prevents optimal participation and gains during rehabilitation, and patients respond poorly to medication [6]. The etiology of CPSP appears to result from an interplay of psychosocial factors (eg, mental health, coping, and social support) [7] and neurophysiological factors (eg, stroke-related damage in corticospinothalamic pathways) [8], suggesting a biopsychosocial etiology. This seems to echo the hyperconnectivity of cognitive emotional brain networks (eg, default mode network [DMN], salience network [SN], and frontal parietal network [FPN]) in chronic pain [9]. Overall, pain after stroke is underresearched [3] and is perceived by patients as an unmet need [10]. Also, health care providers report organizational barriers (eg, insufficient human resources, infrastructure, training) to implementing stroke rehabilitation guidelines [11], which calls for the development of innovative, cost-effective pain management interventions for stroke survivors [12].

Virtual reality (VR) encompasses immersive human-digital interaction technologies [13]. VR seems to be effective in pain management [14] and a viable way to avoid the detrimental effects of opioid-centered analgesia plans [15]. VR technologies can enhance the efficacy of established behavioral interventions by standardizing the presentation of images, instructions, and environmental sounds that accompany behavioral exercises and by increasing the accessibility of practice (eg, patients can use it at home, at their own pace) [16]. VR also seems to be a feasible delivery method of meditation-focused behavioral interventions, which promote a decrease of pain sensitivity by decoupling executive and pain-relevant brain regions (eg, somatosensory cortex) [17]. Additionally, VR poststroke behavioral interventions appear to enhance rehabilitation compliance due to the diverse virtual experiences offered during therapy and the potential for gamification [18]. However, its effectiveness remains inconclusive in terms of clinical validity, as most studies focus on experimental pain [19] and/or fail to adhere to sound randomized controlled trial standards (eg, lack of placebo-controlled studies) [20]. Also, the integration of self-report psychological processes and neurophysiological assessment is still incipient in VR’s efficacy studies in pain management [21].

Acceptance and commitment therapy (ACT) is a third-wave cognitive behavioral approach that promotes awareness and acceptance of internal experiences (eg, thoughts, emotions, physical sensations), and engagement with valued activities, through mindfulness and behavioral exercises [22]. ACT is especially helpful in managing chronic health conditions, as its primary focus is not on changing symptoms, but rather on promoting acceptance of difficult internal experiences and making behavioral changes towards a valued and meaningful life. Stroke survivors find ACT helpful in promoting acceptance and adjustment to stroke limitations, in fostering a sense of safety, and in developing self-regulatory skills [23]. ACT seems to lead to reductions in the triple network connectivity involved in pain chronicity, namely brain networks related to self-reflection (DMN), emotion (SN), and cognitive control (FPN) [24]. Although ACT is feasible and effective in reducing psychopathology in stroke survivors [25], its feasibility in CPSP management is yet to be explored. Additionally, although ACT has been found effective in pain management using technological formats (eg, online platforms, mobile apps) [26,27], ACT through VR has not been extensively tested. One recent study suggests ACT through VR is feasible and effective in improving mental health [28]. However, most VR interventions have been almost exclusively focused on exposure techniques or breathing meditation practices [29], rather than full psychological programs that promote emotional self-regulation skills (eg, attentional regulation) and reduction of avoidant-focused behavior (eg, commitment to valued action), and lack methodologically sound designs (eg, placebo-controlled).

## Methods

### Study Objectives

This project has 2 objectives: (1) we aimed to develop and test the feasibility of an 8-week VR-ACT program in a sample of patients with CPSP. By “feasibility,” we mean feasibility in practice, that is, the extent to which the VR-ACT program can be delivered, measured by *retention* and *acceptability* of the recruitment and intervention implementation phases [30]. (2) We aimed to pilot test the efficacy of VR-ACT in improving pain, mental health, and adaptive psychological processes and skills and in reducing the functional connectivity of the triple network (DMN, SN, and FPN).

### Design

** **The current project will conduct a parallel-group randomized controlled trial design and will follow a multimethod approach (qualitative and quantitative assessments) to assess the feasibility of the VR-ACT delivery [31]. The experimental condition (EC): the VR-ACT program: 8 modules of 3D immersive skills training (2 targeting awareness regulation skills; 3 promoting acceptance; 3 focused on behavioral change and commitment to valued action). To assess the preliminary efficacy and control for possible placebo effects, the control condition (CC) will consist of 8 nonimmersive 2D distracting video animations delivered through a VR headset (Sham VR). Participants in both conditions will use the VR devices throughout 8 weeks. Each module will be available weekly in both conditions and have a duration of 20 minutes. Participants in the CC will be able to use the VR-ACT after the final assessment (see Figure 1).

**Figure 1. F1:**
[figure not shown]
Flowchart of participants. ACT: acceptance and commitment therapy; CC: control condition; EC: experimental condition; VR: virtual reality.

 During the development of the VR-ACT intervention, a patient and public involvement group will be formed to monitor the adaptation of the exercises into VR and their tailoring for patients with CPSP. The group (n=5) will consist of 1 medical doctor and 1 nurse working in CPSP rehabilitation, 1 clinical psychologist specializing in contextual behavioral approaches to chronic pain, and 2 patients with CPSP (1 male and 1 female). The research team and the patient and public involvement group will gather monthly during the development of the VR-ACT intervention to ensure the patient-centered adaptation of exercises is successful and acceptable.

### Participants

#### Eligibility Assessment

 The study will be conducted in adults diagnosed with CPSP who attend the Neurology Service, Pain Unit, and/or the Rehabilitation Service at the ULS-Coimbra, Portugal. Inclusion criteria include (1) medical diagnosis of CPSP conducted by a medical doctor collaborating with the research team, (2) age between 18 and 80 years, (3) implicit de facto internet and computer literacy, and (4) willingness to comply with the study procedures. Exclusion criteria include (1) currently with active malignancy, (2) severe cognitive impairment, (3) currently undergoing any psychological intervention or VR-delivered pain management program, (4) current severe psychiatric symptoms (ie, psychosis, severe depression, nonsuicidal self-injury, suicide attempt in the last month), (5) language impairment with severe comprehension deficit, (6) history of photosensitive epilepsy or previous experience of severe simulator sickness, and (7) other neurological conditions (eg, dementia or Parkinson disease).

#### Sample Size Calculation

 The study was powered for a large final timepoint between-group effect size (standardized mean difference=0.8), allowing for a variant autoregressive ρ over 2 measurements (preintervention and postintervention; 1 and 0.8) to accommodate the likely instability of the outcome variable(s). Setting the α at .05 and a minimum of 80% power, a minimum sample size of N=30 is required (EC: n=15; CC: n=15). We used the power.mrmm function from the R “longpower” package, through WebPower. A sample size of 15 to 30 participants is also sufficient to attain saturation in qualitative analyses conducted through interviews [32].

 To minimize dropout, (1) 2 phone calls will occur during the VR-ACT implementation to address questions on the VR-ACT content. (2) We also expect minor technical difficulties when using the VR headset. At the beginning of each module, an avatar therapist will provide a welcome message, reminding you of the research team’s contact information in case of any technical problems. Before the implementation, an online group meeting will be conducted to introduce the VR headset to participants in both conditions and help with navigation. (3) To promote engagement, weekly emails will be sent to all participants reminding them to use the VR headsets. Also, after the VR system registers 3 days of absence, automatic reminders will be sent to the participants' emails.

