The current study has some potential limitations that should be considered. Due to its feasibility focus, the study is powered for a small sample size (N=30), which limits the statistical power to detect small effect sizes and also restricts the ability to draw definitive conclusions regarding the efficacy of the VR-ACT intervention. Additionally, although an effort will be made to control for the placebo effect with a sham-VR condition, controlling for expectancy and placebo effects in VR interventions remains challenging, and it can be anticipated that participants may still distinguish between conditions despite our efforts to mask the condition allocated. Finally, the generalizability of the expected results can be hindered by strict eligibility criteria. For example, the inherent technological literacy required to participate, as well as the absence of severe psychological and neurological disorders, may limit the applicability of the results to the broader CPSP population.

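### The stated minimum of N=30 for 80% power at a final-timepoint SMD of 0.8 does not follow from the stated inputs: they lead to about 50–62 or about 20–22 in total, depending on what "over 2 measurements (preintervention and postintervention; 1 and 0.8" means

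*Protocol article*

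**What the plan says.** Methods, Sample Size Calculation, names the target as a "large final timepoint between-group effect size (standardized mean difference=0.8"), with an autoregressive ρ "preintervention and postintervention; 1 and 0.8) to accommodate the likely instability of the outcome variable(s"). The alpha is given as "Setting the α at .05", and the power and the result as "a minimum of 80% power, a minimum sample size of N=30 is required (EC: n=15; CC: n=15"). The software named is the mixed-model repeated-measures power function of the longpower package, run through WebPower. The section gives no sidedness and no dropout rate; it lists only measures to limit dropout. Data Collection confirms 30 participants in all, in three waves of 10.

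The section Data Analyses: Feasibility and Preliminary Efficacy plans a linear mixed model of change over time, moderated by allocation.

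The limitations paragraph of the Discussion (Expected Scientific Contribution of VR-ACT) says "the study is powered for a small sample size (N=30), which limits the statistical power to detect small effect sizes", and adds that the sample restricts definitive conclusions about efficacy.

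**The concern.** The section gives an effect size, an alpha, a power and a number of visits, and presents 30 as what they require. A reader should be able to get from the inputs to the output. A two-group comparison at one timepoint with an SMD of 0.8 needs roughly 25 per arm, so 15 per arm looks too few. A strong pre-post correlation can lower the requirement, but only if the analysis uses baseline, and the target is described as a final-timepoint effect. The pair (1, 0.8) is also hard to interpret: it is called a correlation parameter and justified by instability, yet a correlation of 0.8 indicates stability.

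At stake is how the efficacy results will be read. The Discussion expects VR-ACT to be significantly better than sham, and the results are meant as a reference point for a larger multicentre study. The limitations paragraph concedes low power for small effects. If the powered contrast is the unadjusted one, a true SMD of 0.8 would be missed about 44% of the time (100% − 56%).

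**Working it through.** **Inputs.** From Sample Size Calculation: SMD d = 0.8 (SD = 1), alpha .05, power 0.80, two visits, the pair (1, 0.8), 15 per arm. Assumed: two-sided alpha (z = 1.960; z = 0.842 for 80% power); one-sided is also tried.

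**1. The plan's figure: final-timepoint contrast, complete data.** With both visits observed for everyone, the group difference at T1 in the mixed model has variance 2σ²/n, and the correlation cancels.

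n per arm = 2(1.960 + 0.842)²/0.8² = 2 × 7.849/0.64 = 24.5, so 25 per arm, N = 50. With the t distribution it is 26 per arm, N = 52. The stated 30 is not reproduced.

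Power at 15 per arm: noncentrality 0.8 × √(15/2) = 2.19. This gives 56.2% (t, 28 df) or 59.1% (normal). The SMD detectable with 80% power is 1.06 (t). One-sided alpha does not close the gap: N = 40–42, and power at 15 per arm is 69% (t) or 71% (normal).

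**2. The pair read as retention (100% at T0, 80% at T1).** The variance is multiplied by φ = (1 − ρ²)/0.8 + ρ², and n per arm = 24.53 × φ. Power uses the normal approximation.

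| ρ | φ | n per arm | N | power at 15 per arm |
|---|---|---|---|---|
| 0 | 1.25 | 30.7 | 62 | 50% |
| 0.5 | 1.1875 | 29.1 | 60 | 52% |
| 0.8 | 1.09 | 26.7 | 54 | 56% |
| 0.9 | 1.0475 | 25.7 | 52 | 57% |

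**3. The pair read as a pre-post correlation that the analysis uses.** The effective SMD is 0.8/√(1 − ρ²) for a baseline-adjusted contrast and 0.8/√(2(1 − ρ)) for a change (time-by-group) contrast. At ρ = 0.8 these are 0.8/0.6 = 1.33 and 0.8/0.632 = 1.26. By the t distribution they need 10 per arm (N = 20) and 11 per arm (N = 22).

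Power at 15 per arm (t) over a range of correlations:

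| ρ | baseline-adjusted | change |
|---|---|---|
| 0.5 | 68% | 56% |
| 0.6 | 75% | 66% |
| 0.7 | 84% | 78% |
| 0.8 | 94% | 92% |

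**4. What would give 30 in total.** Setting n = 15 gives, by normal approximation, ρ = √(1 − 15/24.53) = 0.62 (baseline-adjusted) and ρ = 1 − 15/49.06 = 0.69 (change). By the t distribution the values are 0.66 and 0.72. Two other routes come close: alpha of .05/4 with ρ = 0.8 (15–16 per arm), or 0.8 used twice, as correlation and as retention (22/0.8 = 27.5, so 28 in total). The section states none of these.

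**The case against.** The strongest reply is that the text calls the values an autoregressive ρ, and (1, 0.8) is also what the first row of a two-visit correlation matrix looks like. The planned mixed model of change over time by allocation uses that correlation. With ρ = 0.8 the power at 15 per arm is 92–94%. Even with 12 completers per arm (an assumed 20% loss) it is 84% for change and 88% baseline-adjusted. On this reading the trial does have at least 80% power. This stands, so 56% cannot be given as the power of the planned analysis without a condition. It does not rescue the sentence: on the same reading the minimum is 20–22, not 30, the outcome is stable rather than unstable, and the effect named is at the final timepoint rather than in change.

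A reader might also infer that 30 was a per-arm result reported as a total, because the retention reading gives 26.7–30.7 per arm for ρ from 0.8 down to 0. That is possible but not shown. It rests on reading the pair as retention, a word the sentence does not use, and on a correlation stated nowhere, while other unstated inputs lead to 30 in total. Nor does the document support 20% dropout as a planned figure.

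Finally, this is a pilot with feasibility as its first objective, and the limitations paragraph already warns against definitive efficacy conclusions. That limits the consequence; it does not make the stated calculation correct.

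**Conclusion.** The statement is wrong as written. At the stated inputs the required total is 50–52 (final-timepoint contrast, complete data, any correlation), about 54–62 (80% retention, ρ from 0.8 down to 0), or about 20–22 (ρ = 0.8 used by the analysis). None is 30. The corresponding power at 15 per arm is about 56–59%, 50–57% or 92–94%. These figures assume two-sided testing, equal allocation and a common SD.

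The document does not settle which reading was meant, so a flat claim that the trial has only 56% power would go too far: that figure holds for a contrast that gains nothing from baseline, or for a change contrast at ρ = 0.5. What can be said is that power for a large effect depends heavily on a correlation that has not been clearly stated. Unless that correlation is about 0.66 or higher (baseline-adjusted) or 0.72 or higher (change), by the t calculation, 15 per arm falls short of 80%.

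**What to change.** - Keep N=30 and justify it by the feasibility objectives.
- In Sample Size Calculation, say whether (1, 0.8) is correlation or retention and give the other quantity separately. If it is a correlation, drop or correct the instability rationale. State the sidedness and the contrast.
- Make the powered contrast the one in the data analysis section: change over time by allocation, or a baseline-adjusted difference if that is what will be fitted.
- Replace the 80% sentence with the power at 15 per arm, given conditionally: about 56% for an unadjusted final-timepoint contrast (detectable SMD about 1.06), and about 68% to 94% baseline-adjusted for ρ from 0.5 to 0.8. If the change contrast is kept, the range is 56% to 92%. Label any dropout figure as an assumption; for example, 12 completers per arm gives 47% unadjusted.
- Extend the limitations sentence to say that, unless the pre-post correlation is high, large effects may also be missed.

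The cost is a rewrite of two paragraphs and possibly a less favourable power statement. No patients, visits or measurements are added. The article says that recruitment had not started, so the correction can be made beforehand if that still holds.

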#### Data Collection

The research team members, who are physicians at the Neurology Service, the Pain Unit, and/or the Rehabilitation Unit of ULS-Coimbra, Portugal, will invite participants and inform them of the aims and conditions for participation. Those who provide written informed consent will be screened for medical eligibility. Then, psychological eligibility will be individually assessed, online and at a time preferred by participants, by the clinical psychologists of the research team, for severe neurocognitive and psychiatric symptoms (using Mini Mental State Examination and a semistructured clinical interview adapted from Structured Clinical Interview for DSM). Those who meet criteria for severe psychiatric disorders and/or cognitive impairment will be excluded from the study, given feedback, and advised to seek medical/psychological consultation. Eligible participants will receive the link to the online preintervention assessment (T0) self-report protocol. A task-oriented (see Section B in Multimedia Appendix 1) functional magnetic resonance imaging (fMRI) will be scheduled to collect preintervention data on the functional connectivity of the triple network (DMN, SN, and FPN). Participants will then be randomly assigned by a member of the research team to 1 of 2 conditions (EC and CC) using random permuted blocks to ensure balance in age (via an online randomizer, eg, random.org [35]). Participants will be informed of the starting date via telephone (or alternatively via email). The medical/nursing collaborators and the research team members not involved with the implementation monitoring will be blinded to the allocation. The two conditions will be masked to participants by not explicitly informing whether the content of the VR is 3D (VR-ACT) or 2D (Sham VR), with both being delivered through the same model of VR headset (MetaQuest 3.0). Nevertheless, for ethical reasons, the two conditions in the study are described in the patient information sheet. A scheduled meeting in the ULS-Coimbra will be held to provide headset devices to participants. Three groups or waves of recruitment and VR-ACT implementations will be conducted (group 1, n=10; group 2, n=10; group 3, n=10; see Figure 1). At the end of implementation, participants will return the devices and will conduct the post-intervention assessment (T1): online psychosocial self-report data collection; and functional connectivity of the triple network data collection (fMRI). Additionally, participants in the EC will be interviewed online by a research team member who is blind to the allocation to collect qualitative data on the acceptability and usability of the VR-ACT (see Section A in Multimedia Appendix 1). The time points of measurements are described in the SPIRIT figure (See Figure 2).

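### Two phone calls are written around the VR-ACT content with no matching calls stated for Sham VR, so the sham may not control for live contact

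*Protocol article*

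**What the plan says.** The measures against dropout are in the second paragraph of Sample Size Calculation:

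- **Phone calls:** "2 phone calls will occur during the VR-ACT implementation to address questions on the VR-ACT content". No recipient is named.
- **Headset introduction:** "an online group meeting will be conducted to introduce the VR headset to participants in both conditions and help with navigation".
- **Weekly reminders:** "weekly emails will be sent to all participants reminding them to use the VR headsets".
- **Absence reminders:** "after the VR system registers 3 days of absence, automatic reminders will be sent to the participants' emails". The arm is not specified.
- **Avatar message:** "At the beginning of each module, an avatar therapist will provide a welcome message". The arm is not specified here. The intervention textbox lists an avatar therapist in the VR-ACT modules.

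The Design section gives the sham the task of controlling for placebo effects, and lets control participants use VR-ACT only once the final assessment is done. VR Program Development describes the sham content as distraction exercises in 2D video. The primary outcomes are pain intensity, pain disability, psychological distress and quality of life, all by participant rating or questionnaire.

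Data Collection plans to mask participants to 3D versus 2D content, using the same headset model in both arms, and adds that "for ethical reasons, the two conditions in the study are described in the patient information sheet". The limitations paragraph of the Discussion concedes that participants may still tell the conditions apart.

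**The concern.** A sham comparison isolates the intended ingredient only if the arms are otherwise treated alike. If one arm is telephoned twice by the study team and the other is not, the contrast is VR-ACT plus staff contact against sham without it. Contact then coincides exactly with allocation, so neither the linear mixed model nor the reliable change index can separate the two.

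The outcomes are ones that attention and support could plausibly move: ratings of pain, disability, mood and quality of life, made by participants whose masking is admitted to be fragile. The calls are also intended to keep people in the study. If they work and reach one arm only, T1 data could be more complete in that arm. With two visits, a participant without T1 contributes only a baseline value, so unequal losses would weaken the comparison further.

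The Discussion expects VR-ACT to be significantly more effective than Sham VR and sees the results as a reference point for a larger trial. An effect partly due to contact would carry over into that planning.

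**Working it through.** The protocol gives no figure for this point, so the main check is textual.

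**Step 1: who can use the calls as described?** Their stated purpose is questions about VR-ACT content. During the 8 weeks only the experimental arm has that content.

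**Step 2: how does the same paragraph write the other measures?**

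| Measure | Arm stated | Live contact |
|---|---|---|
| Two phone calls | None named; purpose tied to VR-ACT content | Yes |
| Headset meeting | Both | Yes, but before the programme starts |
| Weekly emails | Both | No |
| Absence reminders | Not stated | No (automatic) |
| Avatar message | Not stated | No |

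Two measures are explicitly for both arms. The calls are not, and they are the only scheduled live contact described during the 8 weeks.

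**Step 3: is another reading possible?** Data Collection says "Three groups or waves of recruitment and VR-ACT implementations will be conducted", with n=10 in each of three waves. These make up all 30 participants and so include both arms. The phrase about the implementation period therefore does not itself restrict the calls to one arm. The restriction comes from their purpose. If the calls were meant for everyone, sham participants would be telephoned about content they do not have, which would work against the masking. Under either reading the sentence needs to change.

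**Step 4: how much could it matter?** The documents give no contact effect. The following is an illustration under assumption. Let b be the contact effect in SD units, with no true VR-ACT effect and n = 15 per arm. The two-sided 5% rejection probability is

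1 − Φ(1.96 − b/SE) + Φ(−1.96 − b/SE), with SE = s√(2/15).

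- Final value only: s = 1, SE = 0.365.
- Baseline-adjusted, assuming a correlation of 0.8: s = √(1 − 0.8²) = 0.6, SE = 0.219.

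| Assumed b | Share of the 0.8 SD target | Final value only | Baseline-adjusted |
|---|---|---|---|
| 0 | 0% | 5.0% | 5.0% |
| 0.1 | 12.5% | 5.9% | 7.4% |
| 0.2 | 25% | 8.5% | 15.0% |
| 0.3 | 37.5% | 13.0% | 27.8% |
| 0.4 | 50% | 19.5% | 44.7% |

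Example: for b = 0.2 and final values, b/SE = 0.2/0.365 = 0.548, giving 1 − Φ(1.412) + Φ(−2.508) = 0.085.

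The table shows only how sensitive a trial of this size would be. Nothing in the protocol places b at any row, including above zero. Equal calls would change no figure that the protocol states.

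**The case against.** The strongest reply is that one-arm contact is inferred. The protocol names no recipients, it uses the implementation wording for waves containing both arms, and a condensed article may leave the call procedure to a fuller document. This stands as real doubt about who is called. It does not rescue the sentence, because calls about VR-ACT content have no proper use in the sham arm.

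A second reply is that the calls may be part of how VR-ACT is delivered. Assessment of the VR-ACT Delivery lists retention as a measure of that programme, not as a between-arm comparison. That is fair for feasibility: retention with calls is then the relevant quantity. It does not help the efficacy contrast, where the sham is meant to hold non-specific effects constant.

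Third, the Discussion already concedes that expectancy is hard to control and that 30 participants cannot support definitive efficacy conclusions. This tempers the consequences, but the limitation does not mention unequal contact.

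Some stronger readings are tempting and not supported:

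- **That participants are unmasked.** Masking is planned and only conceded to be fallible.
- **That the information sheet reveals a 3D arm with a therapist and a 2D arm.** The sheet is not shown. The protocol says only that it describes the conditions, and that participants are not explicitly told which content is 3D or 2D.
- **That the joint headset meeting lets participants compare arms.** It precedes the programme and covers the headset and navigation. No arm-specific content is said to be shown there.
- **That every other retention aid is stated for both arms.** This is true of the meeting and the weekly emails only.

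**Conclusion.** The point holds as a design weakness that should be corrected before recruitment. As written, and on the natural reading, the two calls give VR-ACT participants scheduled live contact that Sham VR participants do not get, and the sham does not control for it. Differences in the self-reported primary outcomes and in T1 dropout could therefore partly reflect contact.

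This rests on two assumptions: that the calls follow their stated purpose and go to the experimental arm, and that two calls have some effect on self-report or retention. The first is likely but not explicit. The second is unquantified. A reader might infer that the results will be biased towards VR-ACT, or that retention will differ by design. The documents support only that either could happen if the calls are unequal. No size can be given, and the assumed 0 to 0.4 SD range is not an estimate. It also cannot be stretched to cover expectancy arising from the different VR content, which equal calls would not remove.

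**What to change.** In Sample Size Calculation, replace the sentence on the calls with a statement that participants in both arms receive two calls, in the same weeks, at the same planned length and from the same content-neutral script: questions on the assigned content, and technical help. The callers should be staff already involved in monitoring the implementation, so that no blinded team member learns the allocation.

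The cost is 2 × 15 = 30 extra short calls by existing staff. The sample size and the analysis do not change, and the protocol states that recruitment had not started.

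If the sponsor intends the calls as a component of VR-ACT, the protocol should say so and describe the efficacy contrast as VR-ACT with telephone support against sham without it. That costs nothing but leaves contact uncontrolled, so matching the calls is preferable.

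As an option, add one allocation-guess item at T1 in both arms and report it by arm beside the efficacy estimates. It would show how well the masking held. Separate headset meetings by arm are not needed on the evidence in the document.
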